### Harms {17}

We record adverse events and serious adverse events to ensure that any possible harms are detected and monitored appropriately. Reporting of events starts from the point at which the participant is enrolled in the study (i.e. both the consent and baseline procedures have been completed) until the end of their involvement in the study (i.e. the date of the last participant data collection). Adverse and serious adverse events may be detected either via data collection procedures (i.e. researcher assessments and interviews taking place in person or via phone/video call) or via incidental reporting (i.e. researchers may become aware that a trial participant has re-attended the ED while they are on site or be alerted to a potential adverse event by a member of staff in the ED or a participating practitioner). 

The chief investigator (CI) will ensure that safety monitoring and reporting are conducted in accordance with the study procedures. Adverse events and serious adverse events are recorded on a case report form and reviewed by the principal investigator (PI) to determine the relatedness, expectedness, and severity of the events. Any member of staff who becomes aware of an adverse and serious adverse event as described in the protocol must report it to the PIs immediately or the CI and/or sponsor Representative if the PI is not available, with as much information that is available at the time. A research team member can be delegated the task of establishing resolution of the event and completing the protocol-specific adverse event/serious adverse event reporting log. In the event where researchers are unsure of whether an event is considered expected/procedural, they will notify the senior research assistants or trial manager and seek advice.

Summaries of adverse events are periodically (and at least twice a year) presented to the study sponsor, the PMG, the DMC, and the PSC. Serious adverse events which are definitely, probably, or possibly related to participation in the trial and unexpected (RUSAE) are reported to the Research Ethics Committee and the study sponsor within 15 days of the CI becoming aware of the event.

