### Eligibility criteria: if applicable, eligibility criteria for sites and for individuals who will deliver the interventions (e.g. surgeons and physiotherapists) {14b}

The ASSURED intervention is delivered by NHS practitioners working or allied with liaison psychiatry teams (e.g. mental health practitioners, psychiatrists, doctors, support workers, psychologists, nurses, occupational therapists) as well as experienced assistant psychologists and research assistants working or affiliated (i.e. holding honorary contracts) within the participating NHS teams.

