### Intervention and comparator: intervention and comparator with sufficient details to allow replication including how, when, and by whom they will be administered {15a}

Participants in the control group receive usual care. This may involve discharge to the general practitioner, referral or discharge to secondary mental health care, or psychiatric admission. Given the modified study design, it is possible that participants randomised to the control group may have received the standard psychosocial assessment by a practitioner trained in the ASSURED intervention. It is unlikely that these practitioners will deliver the additional ASSURED components (narrative interview, enhanced safety planning) due to time constraints and discharge targets in the ED. In the unlikely event that ASSURED components may be implemented in the control arm in the psychosocial assessment, any impact should be mitigated by randomisation.

Practitioners are trained in the ASSURED intervention. The ASSURED intervention manual is published online (https://assuredstudy.co.uk/manual/). In addition to usual care, the intervention involves rapid follow-up and up to five follow-up sessions over 8 weeks. Sessions are ~50 min long and are delivered flexibly depending on the person’s preference (face to face at the hospital site if a room is available, over the phone, or by video call) with (as far as possible) the same practitioner around 1 week, 2 weeks, 4 weeks, and 8 weeks after randomisation with a fifth optional bank session. These timescales are a guideline and may be used flexibly depending on the availability of the patient and practitioner.

In ASSURED, the use of language and active listening is very important. The training emphasises the importance of human connection, elaboration, validation of distress and help-seeking, and giving hope. Practitioners are trained to stay close to the person’s own words, ask open questions, and wait for people to respond and validate their difficult experiences. Practitioners are trained to use these skills in the therapeutic sessions.

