### Intervention and comparator: criteria for discontinuing or modifying allocated intervention/comparator for a trial participant {15b}

There may be instances where a clinical decision is made for the patient to discontinue their involvement in the study, e.g. services may deem it likely that new mental health practitioners being introduced to a participant’s existing care could be destabilising. It is expected that this will disproportionately affect intervention participants given that there will be more contacts with the study clinicians compared to control participants. If a practitioner or a researcher deems that the patient’s risks have escalated during their participation in the study, then this will be raised immediately with the local principal investigator (PI). A decision will be made as to whether it is appropriate for the patient to continue with the intervention and research assessments. Patients enrolled in the study will still be followed up for the primary outcome (ED reattendance with referral to liaison psychiatry) unless they explicitly request that researchers do not extract their data from the medical records.

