## Methods: monitoring

### Data monitoring committee: composition of the data monitoring committee and its role and reporting structure {28a}

An independent DMC was set up prior to the start of the trial and consists of one independent statistician, one experienced mental health practitioner, and one service user representative. To ensure the credibility of the decisions made by the DMC and for the integrity of the trial, all members of the DMC were invited to declare any competing financial, professional, or scientific interests with the study and the study sponsors. The DMC members have declared no competing interests. The DMC meets at least twice a year and has further email communications as necessary. Meetings are attended by the trial manager, the trial statistician (blinded), and, if necessary, the sponsor representative.

The role of the DMC is to provide advice to the trial team where necessary, advise on protocol modifications, review the accruing trial data, and monitor evidence for treatment harm. To monitor evidence for treatment harm, the DMC is presented with summaries of safety reporting data (adverse events, severity, expectedness, relatedness/causality), and members are not blinded to allocation. The trial statistician does not attend the closed report. The DMC will also assess whether there are any reasons (for example related to the safety of the intervention) why the trial should stop, although there are no formal, predefined criteria for stopping the study. It is customary that the DMC does not make decisions about the trial but rather makes recommendations to the PSC.

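### Adverse events are detected partly through practitioners whose planned contact is with the intervention arm only, so by-arm counts are at risk of bias and should also be shown by detection source

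*Protocol article*

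**What the plan says.** Harms {17} describes two detection routes. One is data collection, that is, "researcher assessments and interviews taking place in person or via phone/video call". The other is incidental: a researcher on site notices a re-attendance, or the researchers may "be alerted to a potential adverse event by a member of staff in the ED or a participating practitioner". Any staff member who becomes aware of an event "must report it to the PIs immediately". Reporting starts once consent and baseline are complete.

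Section {15a} says that, on top of usual care, "the intervention involves rapid follow-up and up to five follow-up sessions over 8 weeks". Sessions last about 50 minutes, at around weeks 1, 2, 4 and 8, and the optional bank session may fall up to 9 months after randomisation. Table 1 places the first scheduled follow-up assessment at 3 months, then 9 and 18 months, in both arms. Section {15b} expects clinical discontinuations to fall more heavily on the intervention arm, because "there will be more contacts with the study clinicians compared to control participants".

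The process evaluation adds further qualitative interviews in the intervention group. In section {28a}, "the DMC is presented with summaries of safety reporting data", members are unblinded, and there are no predefined stopping criteria.

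**The concern.** A comparison of adverse events between arms can be read at face value only if an event has the same chance of being recorded in either arm. Here one named route runs through people who see intervention participants repeatedly by design and must report what they learn. The article describes no matching contact for controls. Section {15b} recognises the unequal contact when it discusses discontinuation, but Harms {17} does not carry the thought over to detection.

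At stake is how the harms data can be read, by the DMC during follow-up and in the final report. With equal true rates the intervention could look more harmful than usual care. A real excess could equally be put down to closer observation. Without the detection source on each event, neither reading can be tested.

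**Working it through.** **1. Contact by arm and period (from {15a}, {17}, {22–25a} and Table 1).**

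| Period after randomisation | Intervention arm | Control arm |
|---|---|---|
| Weeks 1 to 8 | Sessions at about weeks 1, 2, 4 and 8 with staff who must report; incidental routes through ED staff and on-site researchers | Incidental routes through ED staff and on-site researchers |
| 3, 9, 18 months | Scheduled assessment | Scheduled assessment |
| Up to 9 months | Optional bank session | None described |
| Qualitative phase | Additional interviews | None described |

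Text messages at 1 and 2 months ask consenting participants about self-harm, but Harms {17} does not name them as an adverse-event source. An early control event that does not come back through the ED therefore depends largely on recall at the 3-month assessment, and on that assessment taking place.

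**2. Size.** The document gives no adverse-event rate and no detection probability, so there is no stated figure to reproduce on this point. Everything below is illustration on assumed values. The only design figure used is 310 per arm from Sample size {19}. It reproduces: 30% versus 20%, two-sided 5%, 80% power gives 294 per arm. With ICC 0.01 and 12 patients per cluster (carried over from the original design, an assumption) in the intervention arm only, the design effect is 1 + 11 × 0.01 = 1.11, and 2 × 294 × (1 + 1.11)/2 = 620.3, against the stated 620.

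Let d be the probability that an event is detected through routes shared by both arms, and a the probability that practitioners pick up an event the shared routes missed, in the intervention arm only. With equal true risk:

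recorded ratio = [1 − (1 − d)(1 − a)] / d

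With a true risk of 30% in both arms (93 of 310 with an event), c = 0.30 × d is the recorded proportion in controls and i = c × ratio that in the intervention arm. The chance of a nominally significant excess against the intervention is Φ[(i − c − 1.96 × SE0)/SE1], where SE0 is the pooled and SE1 the unpooled standard error. With equal detection it is 2.5%.

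| d | a | Recorded, control | Recorded, intervention | Ratio | Chance of nominal excess |
|---|---|---|---|---|---|
| 0.95 | 0.25 | 88 | 90 | 0.9625/0.95 = 1.01 | 3% |
| 0.80 | 0.25 | 74 | 79 | 0.85/0.80 = 1.06 | 6% |
| 0.60 | 0.25 | 56 | 65 | 0.70/0.60 = 1.17 | 15% |
| 0.60 | 0.50 | 56 | 74 | 0.80/0.60 = 1.33 | 45% |
| 0.40 | 0.50 | 37 | 65 | 0.70/0.40 = 1.75 | 86% |

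**3. A check on timing.** The core sessions span 8 of about 78 weeks, roughly 10% of follow-up. If events were spread evenly, d were 0.50, and practitioners caught every otherwise missed event in those 8 weeks, detection would rise to 0.50 + 0.50 × 0.10 = 0.55, a ratio of 0.55/0.50 = 1.1. Events concentrated soon after the index attendance, the bank session, or disclosure of past events in a session would raise this.

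**The case against.** Several points on the other side are sound.

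- A reader might infer that practitioners see only one arm. The document does not say so. They include "NHS practitioners working or allied with liaison psychiatry teams", and "participants randomised to the control group may have received the standard psychosocial assessment by a practitioner trained in the ASSURED intervention". That index assessment comes before adverse-event reporting starts under the current design, but a control who re-attends may meet the same team. ED staff and on-site researchers can meet both arms. What is one-sided is the planned, repeated contact after randomisation.
- A reader might infer that the routes are pooled and shown to the DMC by arm. Display by arm is a fair inference from unblinded members and a closed report, but neither point is stated. The reporting log and the DMC table layout are not shown, and the log may already hold a source field.
- The direction is likely, not certain. Under {15b}, a clinical decision may also end research assessments, and such decisions are expected more often in the intervention arm. That would lower detection there.
- The most serious outcomes have sources that do not depend on practitioners: deaths and suicide, and ED attendances, from routine records. Table 1 places these extractions after 18 months, however, so they may not help the DMC during the trial.
- A reader might infer that a false signal could stop the intervention. This now has little force. Recruitment ended in December 2024 and delivery can run to 9 months, which puts its end at about September 2025.
- Removing practitioner-reported events from the comparison could hide distress caused by the intervention, which practitioners are well placed to see.

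These points limit the claim and shape the remedy. They do not remove the asymmetry, which follows from the stated detection routes and the contact schedule.

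**Conclusion.** The concern holds as a risk of bias, not as a demonstrated bias. One stated detection route works mainly in the intervention arm, most strongly before the first assessment that both arms share. By-arm adverse-event counts are therefore not fully comparable, with more recorded events in the intervention arm the likelier result. The size is unknown: the assumed values above give ratios from 1.01 to 1.75, and close to 1 if the shared routes catch most events. The document does not support a firmer figure or a claim that the final harms comparison is biased by a known amount. The conclusion rests on practitioners reporting what they learn, as Harms {17} requires, and on controls having no comparable contact, none being described. Outcomes taken from routine records are outside the concern. This is worth correcting because it bears on how harms can be read and costs little; it does not touch the primary analysis or the sample size.

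**What to change.** - Record on the adverse-event and serious adverse-event log every source that identified each event (scheduled assessment, ED staff, on-site researcher, practitioner, qualitative interview, routine record). Back-fill earlier events where the reports allow.
- Keep the table of all events by arm and add a split by detection source beside it.
- Base the between-arm interpretation on events captured by sources common to both arms: the 3-, 9- and 18-month assessments for the DMC, plus trust and NHS England records for the final report.
- Count a practitioner-reported event in that comparison if a common source also captured it. Show separately the events known only through practitioners or intervention-arm interviews, so that none is lost from view.

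Individual serious adverse-event reporting is unchanged. The cost is one log field, the back-filling and one extra table split. The drawback is that the common-source table leaves out some real events, which remain in the all-events table and the separate listing. Follow-up runs to summer 2026, so the change can still be made before database lock.

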### Participant timeline {18}

A timeline for ASSURED is shown in Table 1.

**Table 1 Tab1:** Schedule of enrollment, interventions, and assessments

	Trial period								
	Enrollment			Post-randomisation (months)					
Timepoint	Pre-randomisation	0	1	2	3	6	9	18	> 18 months post-randomisation
**Enrollment**									
Eligibility screening from liaison psychiatry records	X								
Confirmation of eligibility and informed consent	X Approximately 2 weeks of ED attendance								
Randomisation		X							
**Intervention/comparator**									
**ASSURED intervention** (narrative interviewing & enhanced safety planning session, three solution-focused sessions over 8 weeks, three follow-up letters over 9 months, optional bank session)		X	X	X	X	X	X		
**Treatment as usual**		X	X	X	X	X	X	X	
**Assessments**									
**Research assessment at baseline** (sociodemographic information—gender, country of birth, and ethnic group—physical health conditions, psychiatric diagnosis, previous contact with mental health services, psychiatric hospital admissions, level of education, marital status, type of accommodation, living situation, dependents, employment status, receipt of state benefits, treatment history (including contact with healthcare professionals and general practitioners for self-harm and contact with mental health services), asylum-seeker status, drug- and alcohol-related problems, CORE-OM, BSSI, CSRI, SIX, SWEMWBS, EQ-5D-5L, and experiences of care in accident & emergency)	X								
**Research assessment at 3 months** CORE-OM, BSSI, CSRI, SIX, SWEMWBS, EQ-5D-5L and for participants in the intervention arm, the Helping Alliance Questionnaire					X				
**Research assessment at 9 months** CORE-OM, BSSI, CSRI, SIX, SWEMWBS, EQ-5D-5L							X		
**Research assessment at 18 months** CORE-OM, BSSI, CSRI, SIX, SWEMWBS, EQ-5D-5L								X	
Self-reported self-harm over the past month Via text messages			X	X	X		X	X	
Intervention contacts (including duration and mode of contact)			X	X	X	X	X	X	
Repeat re-attendance to ED with a referral to liaison psychiatry (primary outcome—binary outcome) via NHS Trust Data Download & NHS England									X
All patient attendances to ED for 18 months pre- and post-randomisation via NHS England	X								X
Health care use via NHS England									X
All-cause mortality (including suicide) via NHS England									X

### Sample size {19}

Around 30% of patients attending the ED with self-harm/suicidal ideation re-attend within 18 months. Reattendance rates are similar for self-harm and suicidal ideation presentations [6]. Reducing this by one-third (i.e. from 30% to 20%) would be a clinically important difference.

The original sample size calculation for the trial was based on a cluster-randomised design with practitioners as clusters. A figure of 0.03 for the intracluster correlation (ICC) was assumed based on published literature [30]. This gave a target sample size of 1088 to achieve 90% power at the 5% significance level, assuming 12 patients in each cluster. When the protocol was amended to individual patient randomisation, we also considered clustering in the intervention arm since practitioners are directly involved in delivering the intervention. However, practitioner-level clustering in a trial of a similar intervention with the same primary outcome was negligible [31, 32], suggesting the original figure of 0.03 for the ICC was an overestimate. The revised calculation (conducted blind to any interim results from the trial) assumed a value of 0.01. With the agreement of the PSC, the power was also reduced from 90% to 80% for the revised calculation, giving a target sample size of 620 (310 in each arm). Due to the impact of COVID-19 (i.e. significantly increased pressure on EDs and diverting mental health patients from EDs), this was a pragmatic decision to address difficulties in recruitment given the challenges of conducting research in addition to clinical care in the ED. The calculation was performed using the “clsampsi” package in Stata (Stata Corporation, College Station, TX, USA) [33]. 

### Recruitment {20}

We aim to randomise 620 adult patients who present to the emergency department over 27 months. Patients were invited to participate in the study either at the point of attending the emergency department by a practitioner or shortly after leaving the emergency department by a local NHS researcher. We aim to enrol and randomise patients within 2 weeks of having attended the ED.

## Methods: assignment of interventions

### Randomisation

#### Sequence generation, allocation concealment mechanism, and implementation {21 a, b, 22, 23}

Randomisation is implemented using the randomisation module of the REDCap electronic data capture tools hosted at Queen Mary University of London to ensure allocation concealment. The allocation sequence is generated by an independent statistician at the Pragmatic Clinical Trials Unit, using STATA. Allocation to intervention or control is in a 1:1 ratio and in random block sizes of 4, 6, or 8, stratified by site and type of presentation (self-harm or suicidal ideation). The central team access the REDCap module to determine allocations, which they communicate to researchers at the respective sites who then inform patients.

#### Blinding {24 a, b, and c}

The statisticians and health economists analysing the trial data will remain blind to patient allocation until the Statistical Analysis Plan and Health Economics Analysis Plan have been signed off and the trial database finalised and locked for analysis. The researcher who recruits each patient will be unblinded to the patient’s allocation at the point of randomisation (which is after the baseline assessment). We do not anticipate blinding being an issue for the primary outcome as ED reattendances will be extracted from medical records. Similarly, this should not be an issue for the secondary outcome measures, as the majority are based on direct patient self-report. Participants are not blinded.

## Data collection, management, and analysis

### Data collection methods: plans for assessment and collection of outcomes {25a}

All potentially eligible patients were approached for consent to join the study after ED attendance. The baseline research assessment took place after consent and prior to randomisation. Participants will be asked to complete further assessments at 3-, 9-, and 18-month post-randomisation. A subsample of approximately 30 patients, up to 30 practitioners, approximately 10 carers or trusted others (if available), and up to 10 team managers and local PIs such as liaison psychiatry team managers will be approached for a qualitative interview to explore experiences of receiving/delivering the intervention. Further details about the interviews are presented under section “Process evaluation—qualitative interviews”.

